### Imputation procedure for missing data

We will report the reasons for intervention withdrawal in different randomized subgroups and conduct a qualitative analysis of the reasons. The impact of any missing data on the study results will be assessed by sensitivity analysis of the augmented data sets. Patients who drop out of the trial will be enrolled in the analysis of missing data using modern imputation methods.

### Quality assurance

A diverse study group including the principal investigator, recruiters, physicians, medical laboratory, ethics committee, drug supervision and administration department, data coordinating centre and patients will be established before the study, and all of the team members will be trained to understand the design, purpose, and basic information of the trial. In order to ensure that the procedure of the treatment is of high standard and delivered in accordance with the trial protocol, all physicians of the project team will have a certificate of TCM and at least one year of working experience. Before the beginning of the study, each member of the project team has already completed the study-specific theoretical course and undergone the study-specific practical skills training once a day for a month. All physicians have passed the theoretical and practical assessment.

### Ethics and dissemination

The protocol has been approved by the ethics committee of Zhangjiagang TCM Hospital Affiliated to Nanjing University of Chinese Medicine. This trial has been registered at the Chinese Clinical Trial Registry (ChiCTR2100043415) and conducted in accordance with the Declaration of Helsinki. The results of this trial will be disseminated through publication in peer-reviewed journals.

### Safety

The safety of BSHTD has been clinically confirmed. Baduanjin exercise is considered as the traditional Chinese fitness Qigong, and metformin is considered as the first-line treatment for correcting the insulin resistance of PCOS and is not expected to be associated with adverse events when administered in accordance with a normal daily dose. Nevertheless, all participants will be required to report potential adverse events at each trial point (baseline, during the process of treatment and at the 6 months follow-up). In case of unexpected serious adverse events (SAEs), the patient shall withdraw from the trial at any time and go to the corresponding departments of our hospital for free treatment, and the researchers will closely observe the patients until they recover. All adverse events occurring during the study period will be documented in CRFs. SAEs will be reported to the principal investigator, ethics committee and data coordinating centre within 24 h. The principal investigator is responsible for the management of security reports according to local guidelines. Once the SAEs occur, it will be immediately referred to the ethics committee for review. The ethics committee has the final say on the termination of the trial.

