**Methods/design:**

This is a randomized controlled trial involving 190 participants diagnosed with IR-PCOS. All participants will be randomly allocated into 5 groups: group A will receive metformin; group B, BSHTD; group C, Baduanjin; group D, BSHTD combined with metformin; and group E, BSHTD combined with Baduanjin. One course of treatment lasts 3 months, a total of two courses. The primary outcomes are changes in the homeostatic model assessment of insulin resistance (HOMA-IR) and improvements in the oral glucose tolerance test (OGTT) and insulin-releasing test (INS). The secondary outcomes are improvements in the menstrual cycle, ovulation rate, clinical pregnancy rate, basic serum sex hormone levels, free androgen index (FAI), Ferriman-Gallwey scores, body mass index (BMI) and TCM syndrome scores. The related observation indexes will be collected at baseline, during the process of treatment and at the 6-month follow-up. Simultaneously, close monitoring of possible adverse events will be performed throughout the trial process.

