### Study-specific visits and procedures

All participants will receive 2 courses of treatment lasting for 6 months and will be followed up for 6 months. All participants will attend a total of 6 visits: screening visit, baseline visit, first course visit, end-of-treatment visit, and two follow-up visits. Simultaneously, close monitoring of possible adverse events during the trial process will be performed. A flowchart of this trial is depicted in Fig. 1. The schedule of trial enrolment, intervention and assessment is expounded in Table 1.

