### Statistical analysis

Clinical data of all participants will be disposed in the final statistical analysis based on the intent-to-treat principle to determine the robustness of the evidence. The data processors will be unaware of the specific allocation situation. Basic indicators will be analysed to test the balance of each group at baseline. Comparisons will be processed based on changes from baseline to the end of the intervention and follow-up. The one-sample Kolmogorov-Smirnov test and graphical methods will be applied to test the normal distribution of continuous variables (such as the levels of basic serum sex hormones, HOMA-IR, ovulation rate, clinical pregnancy rate, BMI, FAI, Ferriman-Gallwey scores and TCM syndrome scores), which will be presented as the mean ± standard deviation if normally distributed and as the median with an interquartile range if not normally distributed. A paired *T* test or the Wilcoxon rank test will be used to compare variables within a group from baseline to the end of the intervention. Analysis of variance (ANOVA) with Bonferroni correction will be carried out to compare differences among groups of continuous variables consistent with a normal distribution. Continuous variables that do not meet the normal distribution will be processed by using the Kruskal-Wallis test followed by the Mann-Whitney *U* test. Categorical variables will be analysed by chi-square statistics when appropriate, and Fisher’s exact test will be used to compare discrete variables with fewer than 5 observations. All data analyses will be processed by the Statistical Package for Social Sciences (SPSS) version 25.0. A *P* value < 0.05 with a two-tailed test and mean difference with 95% confidence intervals will be considered statistically significant.

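### An unexpected serious adverse event takes the woman out of the trial, not just off the intervention, so outcome assessments still due would be lost

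*Protocol article*

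**What the plan says.** The rule is in the Safety section: "In case of unexpected serious adverse events (SAEs), the patient shall withdraw from the trial at any time". The same sentence sends the patient for free treatment in the hospital and adds that "the researchers will closely observe the patients until they recover". It mentions neither stopping only the assigned intervention nor continuing the scheduled outcome assessments.

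Four other sections bear on it:

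- **Statistical analysis:** "Clinical data of all participants will be disposed in the final statistical analysis based on the intent-to-treat principle", and "Comparisons will be processed based on changes from baseline to the end of the intervention and follow-up".
- **Imputation procedure for missing data:** "We will report the reasons for intervention withdrawal in different randomized subgroups", and "Patients who drop out of the trial will be enrolled in the analysis of missing data using modern imputation methods". A sensitivity analysis for missing data is also planned.
- **Study-specific visits and procedures:** "All participants will attend a total of 6 visits: screening visit, baseline visit, first course visit, end-of-treatment visit, and two follow-up visits".
- **Abstract, Methods/design:** "The related observation indexes will be collected at baseline, during the process of treatment and at the 6-month follow-up".

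**The concern.** Stopping a treatment and leaving a trial are different events. After a serious adverse event there is often good reason to stop the intervention, but seldom a reason to stop measuring the outcome. The Safety section names only leaving the trial. The section on missing data speaks of withdrawal from the intervention and, separately, of dropping out of the trial, so words for the narrower event were available.

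If the sentence is followed literally, every assessment still due is lost, and lost because of a harm that may be related both to the arm and to the outcome. The main casualty is the end-of-treatment HOMA-IR, since the sample size rests on its fall over two courses of treatment. The end-of-treatment OGTT and insulin-release results, also primary, would be lost with it. Such values may not be missing at random, and imputation from the women who stayed cannot test whether they are.

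The safety record is not at stake: adverse events are still documented, and SAEs are still reported within 24 hours. Only later assessments are at risk.

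**Working it through.** **1. Does any other section keep a withdrawn woman in outcome assessment?**

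| Section | Provision | Restores HOMA-IR or OGTT/insulin-release tests? |
|---|---|---|
| Safety | Treatment and observation until recovery | No |
| Study-specific visits and procedures | Six visits for all participants | Makes no provision for a woman who has been withdrawn |
| Follow-up | Observers enquire into cycles, TCM signs, hyperandrogenism and pregnancy, by phone or message if needed | Glucose and insulin tests not listed |
| Imputation procedure for missing data | Trial drop-outs are imputed | No; this acts after the loss |
| Data Availability | Permission is sought to use the samples and data of those who withdraw | No further assessments mentioned |

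None does. Table 1 is not shown, so I make no claim about which tests each follow-up visit repeats.

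**2. The plan's own allowance for loss (Sample size calculation).** Inputs: 30 evaluable women per arm and 20% attrition.

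- Enrolled per arm: 30 / (1 − 0.20) = 37.5, rounded up to 38. Total: 5 × 38 = 190. Both stated figures are reproduced.
- Losses allowed per arm: 38 − 30 = 8.

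**3. How many women might be affected?** The article gives no SAE rate. Assumed rates of unexpected SAEs across the 190 women give:

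| Assumed rate | Women in total (190 × rate) | Per arm (total / 5) |
|---|---|---|
| 0.5% | 0.95 | 0.19 |
| 1% | 1.9 | 0.38 |
| 2% | 3.8 | 0.76 |
| 5% | 9.5 | 1.9 |

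I therefore take k = 0 to 2 women in an arm as the working range.

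- k = 1: 1/38 = 2.6% of the arm, and 1/8 = 12.5% of its allowance.
- k = 2: 2/38 = 5.3% of the arm, and 2/8 = 25% of its allowance.

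**4. Possible error in the arm mean.** Suppose all 38 are analysed with k values imputed, and each imputed change differs from the true one by d in the same direction. Then

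error in arm mean change = k × d / 38.

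I assume d between 0 and 0.40. The upper end is the pilot mean fall on metformin, and describes a woman imputed at that fall whose HOMA-IR did not change. The pilot difference between the combination and metformin is 0.57 − 0.40 = 0.17.

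| k | d | Error (k × d / 38) | Share of 0.17 |
|---|---|---|---|
| 1 or 2 | 0 | 0 | 0% |
| 1 | 0.40 | 0.0105 | 6.2% |
| 2 | 0.40 | 0.0211 | 12.4% |

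**5. Against sampling error.** With the pilot SDs of change (0.24 and 0.27) and 38 per arm, the standard error of a two-arm difference is √[(0.24² + 0.27²) / 38] = √(0.1305 / 38) = 0.059. The two upper errors are 0.0105 / 0.059 = 0.18 and 0.0211 / 0.059 = 0.36 standard errors.

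**The case against.** The strongest objection is to the reading. A withdrawal forced by an event does not happen *at any time*; that phrase belongs to a right to leave. The article's English is loose elsewhere, and *shall* may stand for *may*. On that reading the sentence is the usual freedom to withdraw and nothing is wrong with it. This possibility stands and cannot be settled from the article. But the text as printed is mandatory, and even the permissive version fails to separate stopping treatment from leaving the trial.

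A second objection is that the Safety section never says remaining visits are cancelled, and that rules for follow-up after discontinuation are detail an article may leave to the full protocol. That would answer a complaint about silence. Here, however, the article states a rule about participation, and the rule names the trial. It is fair to add that the missing-data section defines neither of its two withdrawal terms, so the contrast between them supports the reading without proving it.

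Third, the plan already has an intention-to-treat analysis, reasons for withdrawal by group, imputation, a sensitivity analysis and a 20% attrition allowance. These do limit the damage. The allowance, though, protects power and not against bias, and imputation is second best to a value that could be measured at a visit already scheduled.

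Fourth, the effect is very small. The upper figure needs two unexpected SAEs in one arm, both imputed wrongly by 0.40 in the same direction, with no offset in the comparison arm. This is correct, and it limits the point to minor severity.

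**Conclusion.** The concern holds as a minor point about a badly fixed rule. As written, an unexpected SAE ends participation in the trial, and nothing else in the article keeps the woman in assessment of the primary outcomes. The loss would be avoidable and linked to harm. It weakens the intention-to-treat comparison but does not contradict it.

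The likely size is from nothing to an error of about 0.021 in an arm's mean HOMA-IR change, or roughly a third of a standard error of a two-arm difference. That rests on two assumptions the article cannot confirm: 0 to 2 affected women per arm, and an imputation error of 0 to 0.40 each. The error is proportional to both, so it can be rescaled for other values. No conclusion of the trial is likely to turn on it, and the sample size need not change. Confidence is medium, because the sentence may have been meant permissively.

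**What to change.** Replace the withdrawal clause in the Safety section with one sentence, for example: *After an unexpected serious adverse event the assigned intervention may be stopped on clinical grounds; the participant remains in the trial and attends her remaining scheduled assessments, including HOMA-IR, OGTT and the insulin-releasing test at the end of treatment, unless she withdraws consent.*

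This keeps the clinical protection and the right to leave, and it is unambiguous whichever meaning was intended. The cost is that a few women attend visits after an SAE. Those visits are already scheduled, and the section on patient and public involvement says study funds cover the laboratory tests.

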## Discussion

As far as we are aware, no previous investigation has discussed whether Baduanjin exercise has therapeutic potential in IR-PCOS. Our research is the first randomized controlled trial to compare the efficiency of a combination of TCM and behavioural therapy in the treatment of IR-PCOS. Each aspect of this trial was fully discussed by the research group, and this protocol was unanimously approved by the group. The assumptions of this trial are as follows: Bushen Huatan Decoction shows equivalent clinical effects as the single-use of metformin; the efficiency of Bushen Huatan Decoction combined with metformin is superior to that of a single-use of metformin; the efficiency of Bushen Huatan Decoction combined with Baduanjin exercise is superior to that of Bushen Huatan Decoction and Baduanjin exercise; and the efficiency of Bushen Huatan Decoction combined with Baduanjin is equal to that of Bushen Huatan Decoction combined with metformin.

From the perspective of TCM syndrome differentiation and treatment, kidney deficiency and phlegm dampness are mainly responsible for the pathogenesis of IR-PCOS, so the central focus of treatment should be on tonifying the kidney, invigorating the spleen and reducing phlegm, while paying attention to lifestyle modification in the course of treatment. It is worth noting that patients with IR-PCOS appear to have a higher risk of irregular diet and lifestyle. However, taking weight-loss drugs for a long time is not a sustainable solution for overweight patients; from this, we developed a comprehensive intervention program that combines TCM with Chinese fitness Qigong Baduanjin for the treatment of patients with IR-PCOS. On the one hand, a lifestyle-based intervention program can provide considerable benefits, such as body weight loss and improvements in physical signs of hyperandrogenism. On the other hand, the program can improve the psychosocial status of patients and provide a better quality of life. Additionally, a social network platform will be established to motivate and encourage the patients throughout the intervention and follow-up phases.

In summary, the aim of this trial is to conduct a pragmatic study that is expected to provide reliable evidence for using TCM-behaviour intervention therapy in future clinical practice in IR-PCOS and promote the application of Chinese fitness Qigong Baduanjin in the treatment of lifestyle diseases. We consider that this trial will contribute significant information for further recommendations regarding lifestyle interventions in females with IR-PCOS.

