### Sample size calculation

The sample size calculated by Power Analysis & Sample Size (NCSS-PASS 11.0) was assessed based on HOMA-IR, which is the most significant outcome in this trial. In our pilot study (according to the research results of [name] doctoral thesis) evaluating the effect of metformin and BSHTD on HOMA-IR in patients with IR-PCOS, the results showed that HOMA-IR decreased from 2.11±0.30 to 1.71±0.26 in the metformin treatment group and the difference before and after treatment was 0.40±0.24, while HOMA-IR of Bushen Huatan Decoction combined with metformin treatment group decreased from 2.09±0.30 to 1.52±0.26 and the difference before and after treatment was 0.57±0.27. Therefore, we used the minimum sample size required to evaluate effectiveness [18]. We anticipate that after two courses of treatment, HOMA-IR of Bushen Huatan Decoction combined with metformin group will decrease by 30%, and HOMA-IR of single-use of metformin group will decrease by 20%. Therefore, the difference is 10%,with two-sided α assigned to be 5% and *β* 20% at the upper limit, respectively, at which the power is 90% and the rate of attrition estimated to be 20%. In a one-way ANOVA study, sample sizes of 30, 30, 30, 30, and 30 were obtained for the 5 groups whose means are to be compared. A total sample size of 150 subjects achieves 90% power to detect differences among the means versus the alternative of equal means using an F test with a 5% significance level. By enrolling 38 participants in each group, we allow the rate of attrition to be estimated to be 20%.

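### Two equivalence hypotheses (BSHTD v metformin; BSHTD+Baduanjin v BSHTD+metformin) have no margin, and a plan sized and analysed only for differences cannot establish them

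*Protocol article*

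**What the plan says.** The Discussion sets out five comparisons as the assumptions of the trial. Two are claims of sameness. For group B against group A: "Bushen Huatan Decoction shows equivalent clinical effects as the single-use of metformin". For group E against group D: "the efficiency of Bushen Huatan Decoction combined with Baduanjin is equal to that of Bushen Huatan Decoction combined with metformin". The other three are superiority claims: E over B, E over C, and D over A, the last worded as "the efficiency of Bushen Huatan Decoction combined with metformin is superior to that of a single-use of metformin". The authors therefore use different words for the two kinds of claim.

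The Statistical analysis section plans this for between-group comparisons of normally distributed outcomes: "Analysis of variance (ANOVA) with Bonferroni correction will be carried out to compare differences among groups of continuous variables". Other continuous outcomes are "processed by using the Kruskal-Wallis test followed by the Mann-Whitney" U test. The only decision rule is a two-tailed P below 0.05, to which the interval estimate is attached: "mean difference with 95% confidence intervals will be considered statistically significant". The interval is not compared with any margin.

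The Sample size calculation section starts from the pilot contrast between BSHTD plus metformin and metformin alone. It uses a one-way ANOVA F test for differences among five means, at 5% significance and 90% power. The result is 30 per group, or 38 after allowing for 20% attrition.

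**The concern.** A test for difference puts equality in the null hypothesis, and failing to reject that null is not evidence for it. To conclude that two treatments are equivalent, one must fix how large a difference would still count as equivalent and show that the data exclude anything larger. The protocol states two such conclusions as hypotheses but gives neither that limit nor a rule for applying it. The number of patients was not derived for that purpose either.

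E against D carries the most weight. Group E is the title intervention, and the abstract expects it to become an alternative treatment for IR-PCOS. A finding that it equals BSHTD plus metformin would support Baduanjin in place of metformin alongside the decoction. If a non-significant comparison were taken as that finding, a materially worse arm could pass. The Bonferroni correction would make this more likely: it guards the superiority claims but raises the share of comparisons that come out non-significant.

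**Working it through.** **Inputs.** All are from the Sample size calculation section unless marked.
- Fall in HOMA-IR: metformin 0.40 (SD 0.24); BSHTD plus metformin 0.57 (SD 0.27).
- Pilot difference: 0.57 − 0.40 = 0.17, which is 0.17/0.40 = 43% of metformin's own fall.
- Pooled SD: √((0.24² + 0.27²)/2) = 0.255.
- 30 evaluable and 38 enrolled per arm.
- Assumed: a second deficit of 0.10, a quarter of metformin's fall; and Bonferroni over 5 pairs (those named in the Discussion) or 10 pairs (all pairs of five groups). The protocol does not give the number of pairs.

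**Reproducing the planned size.** The protocol does not give all five means. Taking A = B = C = 0.40 and D = E = 0.57, the noncentrality is 30 × 0.03468/0.2554² = 15.9 on 4 and 145 df. Power is then 90.1%, and 30 is the smallest n that reaches 90%. Attrition: 30/0.8 = 37.5, so 38 per arm and 190 in total. This pattern is not the only one that gives 30 (one group differing by 0.21 also does), but in every case the calculation is for detecting differences.

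**Chance of a non-significant result when a real deficit exists.** The standard error of a pairwise difference is 0.2554 × √(2/30) = 0.0660. The noncentrality is δ/SE: 0.17/0.0660 = 2.58 and 0.10/0.0660 = 1.52. The probability is the noncentral-t mass between the two critical values. Each range at 30 per arm runs from the pooled ANOVA error (145 df) to a two-group t test (58 df).

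| True deficit | Unadjusted | Bonferroni, 5 pairs | Bonferroni, 10 pairs |
|---|---|---|---|
| 0.17, 30 per arm | 27-28% | 51-53% | 60-62% |
| 0.10, 30 per arm | 68% | 86% | 90-91% |
| 0.17, 38 per arm | 18% | 38-40% | 47-49% |
| 0.10, 38 per arm | 60-61% | 81-82% | 87% |

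**Width of the interval.** At 30 per arm the 95% half-width is 2.002 × 0.0660 = 0.13, a third of metformin's 0.40 fall. With Bonferroni over 10 pairs it is 2.851 × 0.0660 = 0.19, wider than the 0.17 pilot difference.

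**What a proper equivalence test could deliver.** This is two one-sided tests at 5%, with true difference 0, SD 0.255 and 30 per arm. The margins are illustrative, since the document gives none.

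| Margin | Power at 30 per arm |
|---|---|
| 0.17 | 63% |
| 0.15 | 45% |
| 0.13 | 24% |
| 0.10 | 1% |

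The last figure follows from the 90% half-width, 1.672 × 0.0660 = 0.11, which already exceeds a margin of 0.10. By the normal formula n = 2[SD(z₀.₉₅ + z₁₋β/₂)/margin]², 80% and 90% power need 39 and 49 evaluable per arm at a margin of 0.17, and 112 and 142 at 0.10.

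**The case against.** A reader might infer that the protocol intends to read P > 0.05 as equivalence. It does not say so. The Statistical analysis section says what counts as significant and is silent on how a non-significant result will be interpreted. It also plans a mean difference with a 95% CI, the quantity on which an equivalence judgement would rest. That part of the objection stands: what is missing is the margin, and the misuse is a risk to be closed off, not a stated plan.

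It can also be said that the two statements are expectations placed in the Discussion, that the Study design section describes a search for the best scheme, and that an unseen SAP may hold a margin. The first two are fair readings, but the statements stand in one list with the superiority claims, including the contrast behind the sample size. The SAP could add a margin. It would not change the fact that the article's hypotheses do not fit the sizing, tests and decision rule printed beside them.

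A further inference would be that equivalence would be reached mostly through lack of power. At a deficit of 0.17 without correction this fails, because the test detects it about 72% of the time. It is true only for smaller deficits or under a heavy correction. If dropouts are retained by intention to treat with imputation, the effective size lies between 30 and 38 per arm, and the 38-per-arm rows give the favourable limit.

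**Conclusion.** The point holds as a mismatch between stated parts of the protocol: two hypotheses of sameness, but a sample size, a set of tests and a decision rule that address differences only. Neither hypothesis can be established as planned, and a non-significant comparison would be weak evidence. At 30 evaluable per arm it would occur about 27-28% of the time at a true deficit of 0.17 and about 68% at 0.10 unadjusted, and more often with Bonferroni.

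These figures rest on the pilot SDs, on 30 evaluable per arm and, for the corrected figures, on 5 to 10 pairs. The pilot mean baseline (about 2.1) lies below the trial's entry threshold of 2.29. If women with higher values vary more, the true chances of non-significance would be larger. The deficits and margins are illustrations, not clinical thresholds. The superiority comparisons, D over A and E over B and C, are untouched by this point.

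**What to change.** Reword B v A and E v D, wherever they are stated as hypotheses, as estimation of the difference in HOMA-IR change with a 95% CI. Add one sentence to the Statistical analysis section saying that a non-significant difference will not be reported as equivalence or equality. This costs only wording, with no change to the sample size or conduct.

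If the sponsor wants to keep an equivalence claim, it must fix in advance a clinically justified margin and the rule that equivalence is claimed only when the 90% CI lies wholly inside it (two one-sided tests at 5%). It must also state the low power at the planned size shown above. Raising that power needs more patients. After 20% attrition, 80% to 90% power would need 49 to 62 enrolled per arm at a margin of 0.17 (39/0.8 and 49/0.8), and 140 to 178 at 0.10 (112/0.8 and 142/0.8), against the planned 38.

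The downside of either route at the present size is that equivalence will probably not be claimable.
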